### Successive built up of subprojects 1, 2, 3 and 4 as well as the longitudinal observational cohort study

The identification and cross-sectional assessment of adolescents with extreme obesity in subproject 1 of YES will form the basis for subproject 2 (Randomized controlled manual-based low-level intervention) and subproject 3 (Structured preparation, pre- and post-surgery treatment of adolescents with extreme obesity) of YES. All patients assessed in SP 1, followed up in SPs 2 and 3 will constitute a well characterized cohort of adolescents with extreme obesity. This cohort will be prospectively followed-up with examinations every six months in a longitudinal observational cohort study as part of YES that will cover a maximum of nine years (maximal duration of grant). Thereby, we will gain insight into the course of adolescent extreme obesity and the development of the medical and psychosocial comorbidities during adolescence and young adulthood. We will perform subgroup analyses based on the treatment options these youths have chosen. We will determine the percentage of patients who can be integrated into the job market or into an apprenticeship training position. Finally, in subproject 4 “Economic aspects of extreme obesity in adolescents” of YES we will analyze the economic burden of extreme obesity in adolescents.

### Subproject 2

In SP 2 “A Structured, manual-based low-level intervention vs. treatment as usual Evaluated in a randomized controlled trial for adolescents with extreme obesity – the STEREO trial” of YES we propose a new innovative low level intervention to overcome treatment abstaining behaviour. The new intervention will not focus on weight loss. We will evaluate efficacy and safety of the new intervention in comparison to treatment as usual. The RCT will be conducted according to “good clinical practice” and is professionally supported by the Center for Clinical Trials Essen.

The new innovative intervention will be a manual based low key group intervention with 6 sessions over the course of 3–6 months focusing on the improvement of quality of life and psychosocial functioning. The topics covered are: social competency, body image, coping with weight related stigmatization, victimization and bullying, coping with stress, life satisfaction, and psychological well being. The intervention does not primarily focus on weight loss.

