The active comparator (“treatment as usual”; TAU) is a manual based group intervention as proposed by the treatment guidelines in Germany for routine obesity care. The 6 sessions over the course of 3–6 months focus on weight loss. The topics covered are causes, consequences and treatment options of obesity, nutrition, eating behaviours and problem solving strategies, self esteem and emotional eating, physical activity and exercise, media usage.

Based on the current state of knowledge, we will perform a confirmatory test of two *a priori* hierarchically ordered hypotheses controlling the family-wise significance level α (two-sided) at 5%
[34]. The primary research questions are:

1. The compliance rate 6 months after randomization differs between subjects in the new low key intervention group compared to the TAU group.

2. Covariant-adjusted changes in health-related quality of life (HRQoL) (assessed by the DISABKIDS scale; Chronic Generic Module) between baseline and the 6 months follow-up will be different in the low key intervention group compared to the TAU group.

The sample size calculation was driven by the second of the two research questions reflecting empirical evidence on standardized effect sizes from the literature (e.g.
[35] and the presumed smaller effect size. However, detailled power considerations also demonstrated that the power will be larger than 80% if the compliance rates differ by more than 15% points for a range of compliance rates under TAU (continuity corrected Chi^2^ test). In terms of null (H_0_) and alternative (H_1_) hypotheses for the second research question we will test: H_0_: Δ_NEW_ = Δ_TAU_ against H_1_: Δ_NEW_#Δ_TAU_ where Δ. is the covariant-adjusted expected (i.e., mean) change in HRQoL between baseline and the 6 months follow-up in the respective group. Two independent groups with 146 adolescents each have a power of 80% to detect mean differences of 0.33 in units of standardized effect sizes (Cohen’s d; *t*-test with equal variances; α = 0.05 (two-sided)). Allowing for ~15% “Drop-outs” we decided to ascertain a total 2 × 175 = 350 adolescents for SP 2 and will screen a total of 1,200 adolescents for the complete YES project based on expectations regarding the participation in subprojects.

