Secondary outcome measures include a responder analysis (combining compliance rate and changes in HRQoL), changes in the 6 subscales of DISABKIDS, changes in quality of life (KIDSCREEN-52), changes in self-esteem (Rosenberg’s scale patient questionnaire), changes in self reported time spent outside the home (questionnaire), changes in depression symptoms (Becks Depression Inventory 2), changes in perceived stress (Fliege scale questionnaire), changes in self reported attendance of school, apprenticeship, or work as well as changes in self reported physician and therapist contacts.

Individuals who complete the baseline evaluations in SP 1 will be invited to participate in 6 group sessions over a 6 months period. Group assignment to the low key intervention vs. standard care group will be at random. The effects of the interventions on health related quality of life and psycho-social functioning will be assessed by questionnaires 6 months after the treatment start. Subsequently, subjects will be invited to participate in SP 3 and the longitudinal follow-up examinations of YES.

### Subproject 3

The aim of the SP 3 “Safety and effectiveness of weight loss surgery in adolescents with extreme obesity within a structured pre- and post-surgery treatment programme – Observational study” of YES is to generate observational data of safety and effectiveness of weight loss surgery in adolescents with extreme obesity.

Adolescents with extreme obesity identified and assessed in SPs 1 and 2, who 1) fulfil the formal criteria for bariatric surgery

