### Longitudinal observational cohort study

All adolescents who participated in the baseline examination (SP1) of YES are to be recruited for a longitudinal observational cohort study that will cover a minimum of nine years. We will gain insight into the natural course of adolescent extreme obesity; we will also perform subgroup analyses based on the treatment options that we originally provided these youths with. We will determine the percentage of patients who can be integrated into the job market or into an apprenticeship training position.

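### The two confirmatory outcomes of Subproject 2 are dated from different origins (randomisation for compliance, treatment start for quality of life), and nothing links the two dates

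*Protocol article*

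**What the plan says.** All the trial statements are in the Subproject 2 section of the protocol article.

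- Primary hypothesis 1: "The compliance rate 6 months after randomization differs between subjects in the new low key intervention group compared to the TAU group". The origin is randomisation.
- Primary hypothesis 2: adjusted change in HRQoL (DISABKIDS) "between baseline and the 6 months follow-up will be different in the low key intervention group compared to the TAU group". No origin is named for the six months.
- Procedure, at the end of the section: effects on HRQoL and psychosocial functioning "will be assessed by questionnaires 6 months after the treatment start". The origin is treatment start.
- Course length, new intervention: "6 sessions over the course of 3–6 months focusing on the improvement of quality of life". Comparator: "The 6 sessions over the course of 3–6 months focus on weight loss". The later invitation text, which covers both arms, says participants "will be invited to participate in 6 group sessions over a 6 months period".

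The two hypotheses are tested in a hierarchical order with compliance listed first. A secondary responder analysis combines compliance with HRQoL change.

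On the observational cohort, the section on how the subprojects build on each other says it will "cover a maximum of nine years (maximal duration of grant". The Longitudinal observational cohort study section describes a study "that will cover a minimum of nine years".

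**The concern.** A fixed-time comparison in a randomised trial needs one origin that exists for everyone randomised. Randomisation is such an origin. Treatment start is not: it happens after allocation, and some participants never reach it.

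Three things follow if the text is applied as written.

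1. A participant who never attends has no date on which the HRQoL questionnaire falls due. Whether HRQoL is observed then depends on uptake. The trial is aimed at adolescents who tend to avoid treatment, and its first hypothesis asks whether compliance differs between arms. Missing HRQoL could therefore be linked to arm through the behaviour under study.
2. For one person, compliance and HRQoL refer to different times unless the first session falls on the day of randomisation. The responder analysis merges the two.
3. If the course takes close to six months and there is any wait before it begins, the compliance date comes before the last session. Compliance is listed first in the hierarchy, so a poorly timed count there also bears on whether the HRQoL hypothesis can be tested confirmatorily.

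The nine-year statements concern the cohort and not the trial's primary tests.

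**Working it through.** **Does this touch the sample size?** Inputs from Subproject 2: standardised difference 0.33, two-sided alpha 0.05, power 80%, 146 per group, about 15% dropout, 2 × 175 = 350.

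- The two-sample t-test needs 145.1 per group, rounded up to 146; power at 146 is 80.2%. The stated figure reproduces.
- 146 / (1 − 0.15) = 171.8, so 172 per group or 344 in total, against 175 and 350 stated. The stated number allows for 1 − 146/175 = 16.6% loss, which fits the approximate 15%.

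The sample size stands and the timing point does not depend on it.

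**Time origins side by side.** Let L be the wait in months from randomisation to the first session. Compliance is taken at month 6 after randomisation and HRQoL at month 6 + L. They coincide only if L = 0. The article gives no value or limit for L, so the range 0 to 3 months below is an assumption. For a participant who never starts, L does not exist, and neither does 6 + L.

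**Sessions held by the compliance date.** Let D be the course length. Assume six equally spaced sessions, the first at L and the last at L + D, so session i (i = 0 to 5) falls at L + D × i/5. All six are held by month 6 only if L + D ≤ 6. D = 3 and D = 6 are the ends of the stated range.

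| L (months, assumed) | HRQoL, months after randomisation | Sessions held by month 6, D = 3 | Sessions held by month 6, D = 6 |
|---|---|---|---|
| 0 | 6 | 6 of 6 | 6 of 6 |
| 0.5 | 6.5 | 6 of 6 | 5 of 6 |
| 1 | 7 | 6 of 6 | 5 of 6 |
| 2 | 8 | 6 of 6 | 4 of 6 |
| 3 | 9 | 6 of 6 | 3 of 6 |

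Example, D = 6 and L = 2: sessions fall at months 2, 3.2, 4.4, 5.6, 6.8 and 8, of which four are by month 6.

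With a 6-month course, any L above 0 leaves at least the last session outstanding. With a 3-month course, every session fits for waits up to 3 months.

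**Cohort duration.** One section makes nine years the ceiling and ties it to the grant; the other makes it the floor. Unless the duration is exactly nine years, both cannot hold. The abstract's Methods/Design paragraph makes follow-up depend on additional funding, which does not fit a floor either.

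**The case against.** The strongest reply is that this is loose wording in a condensed article. The hypothesis itself refers only to a six-month follow-up, the procedural sentence is a one-line summary, and nothing says that non-starters are excluded. Figure 1, which carries the visit timepoints, is not reproduced in the text reviewed and may be clearer. Visit windows and the handling of non-starters normally sit in the full protocol or analysis plan. That is fair as to missing detail. It does not remove the conflict, because the article itself states two origins.

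Several stronger readings are tempting and should not be drawn.

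- A reader might infer that compliance is counted before the sessions were offered. At most it is counted before the last of them, and only with both a wait and a course close to six months.
- A reader might infer that slow filling of groups biases the comparison. The article gives no group size, does not say that groups are closed, and does not say whether randomisation comes before group formation. Any waiting time worked out from recruitment would be guesswork. Waits that are equal in both arms could blur a difference but would not create one.
- A reader might infer that never-starters are in fact left unassessed. The text leaves them without a due date; it does not say they are dropped.
- A reader might treat the two course lengths as a flat contradiction. Six months is the upper end of the 3–6 month range and can be read as the window for the six sessions. This is the weakest of the conflicts.

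The article also does not define the compliance rate. If it is not based on session attendance, the effect of an early cut-off on it does not arise in this form. In either case its size cannot be calculated.

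**Conclusion.** The point holds as a conflict of time origin between the two confirmatory outcomes. Compliance is dated from randomisation and HRQoL from treatment start, with nothing in the article to make them the same. Two consequences follow directly from the wording: randomised never-starters have no HRQoL due date, and the responder analysis combines measurements from different times whenever there is a wait.

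The effect on compliance is conditional. It needs a wait after randomisation, a course close to six months, and a compliance definition based on attendance. Under those assumptions, waits of 0.5 to 3 months leave one to three of the six sessions outstanding at the cut-off; with a 3-month course and the same waits, none is outstanding. No direction or size of bias between arms can be derived from the document, and the sample size of 350 is unaffected.

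The time origin should be settled before the trial data are analysed. The maximum/minimum conflict on cohort duration is real, but it is a separate and minor correction.

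**What to change.** 1. Date both primary outcomes from randomisation, with one common visit window that applies to every randomised participant, including those who never start. Replace the treatment-start wording in the procedural sentence accordingly.
2. Place the compliance cut-off, identically in both arms, at a time by which all six sessions would have been offered. If this is later than month 6, amend hypothesis 1 to match.
3. Reconcile the two statements of course length.
4. Separately, reconcile the cohort duration, for example as up to nine years, depending on funding.

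The cost is protocol wording and the programming of visit windows. If the cut-off moves, follow-up becomes slightly longer for some participants. The sample size does not change, and neither the method of randomisation nor the participant-level form of the compliance outcome needs to be altered.

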[20]. It has been reported that weight loss surgery significantly improved psychosocial functioning
[21], quality of life
[22], and physical function
[23]. In general, gastric banding resulted in less weight loss in comparison to bypass operations.

However, there are several possible complications of weight loss surgery. In adults perioperative mortality rates are 0.1-0.5% and immediate postoperative complications occur in 10% of individuals. Diversionary procedures increase the long-term risk of nutrient deficiency (up to 50% of patients) while gastric bands can slip (6% of patients) or erode (10%) necessitating re-operation
[24].

In adolescents, weight loss surgery is at an experimental stage. Preliminary data in adolescents suggest that short-term outcomes for weight loss and improvement of comorbidities are similar to those observed in adults, but further studies are necessary to confirm these results and evaluate long-term outcomes
[18,25-28]. Early evidence of safety and efficacy exists for two procedures (adjustable gastric band, Roux-en-Y gastric bypass (RYGB))
[15,29-31]. In principle, the group of adolescent patients with extreme obesity may be particularly vulnerable to long-term complications of surgery; on the other hand the group could potentially maximally benefit via for example enhanced integration into the job market and reduction of social isolation.

Although weight loss surgery is still at an experimental stage in adolescents there is currently a significant increase in adolescents being operated
[32]. This is also true in Germany [Lennerz BS, Wabitsch M, Lippert H, Wolff S, Knoll C, Weiner R, Manger T, Kiess W, Stroh C: Bariatric Surgery in Adolescents and Young Adults – Safety and Effectiveness in a Cohort of 345 Patients, submitted]. However, neither structured preparation nor post-treatment follow-up programs currently exist for these patients.

Given the above mentioned challenges, we have identified “Medical and psychosocial implications of adolescent extreme obesity – acceptance and effects of structured care” as an important research issue. We have developed a recruitment approach for adolescents with extreme obesity involving various institutions to which these adolescents have contact to as well as our well established clinical treatment programs and two German registries (APV, CrescNet). We have chosen a synergistic and coordinated activity involving four regional networks (Leipzig (East)

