[15,32,36,37], 2) have shown compliance with either one of the intervention programs (SP 2) and 3) are willing to consider weight loss surgery, will participate in a two month long manual based preoperative information program to ensure that the adolescents know potential risks and benefits. They will then be able to give informed consent (as well as their parents in case of minors). Such adolescents will undergo weight loss surgery in one of the five treatment centers which have all established collaborations with bariatric surgery units. After surgery, the patients will participate in a manual-based post-operative treatment programme. 7From an ethical viewpoint, we will have taken extensive precautions to make sure that the adolescents can give truly informed consent. Because the adolescents will have to complete *both* the low level intervention program outlined in SP 2 and the 2 month long presurgical program, they will be selected for maximal compliance which we consider as the major predictor for a good outcome of bariatric surgery.

We will use standardized techniques and measures to assess the short, medium and long term results of bariatric surgery. We will compare post-surgical outcomes to pre-operative status and examine risks and benefits of surgery. The study will be performed on the basis of the protocols of the US-Teen-LABS study
[38]. As a control group we will examine adolescents with extreme obesity who successfully completed SP 2 and who either declined participation in the pre-surgery program outlined in this proposal or declined surgery after completion of the pre-surgery program using propensity-score methods. A further comparison group is formed by those subjects who take part in SP1 but refuse to participate in the RCT (SP2) if they are available for follow-up investigations.

The following objectives will be assessed: 

1. identification of those extremely obese adolescents best suited for bariatric surgery,

2. developing a structured patient program to be completed prior to and after surgery,

3. use the observational data to generate (potentially biased) effect sizes estimates of safety and effectiveness.

Finally, we will also determine associations between clinical/demographic patient characteristics, components of the surgical procedure with post-operative risks and changes in patient status.

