The primary endpoint of SP3 is weight change defined as difference between BMI at date of surgery and 12 months after. This outcome choice is in accordance with the outcome of the Teen-LABS study. The other secondary outcome measures are change of BMI between date of surgery and after 24 months, changes (date of surgery - 12 months) in somatic and psychosocial co-morbidities of obesity as described in SP 1, and changes (date of surgery - 12 months) in percentage of self-reported probands´ attendance of school, vocational training or work (see SP2).

Perioperative and postoperative safety (adverse and serious adverse events) will be investigated using a standardized protocol
[39] including risks of bariatric surgery, nutrient deficiencies, and adherence to nutritional supplements.

There will be different types of bariatric procedures performed in adolescents with extreme obesity. The course of treatment (preoperative, postoperative, follow-up) as well as the impact on quality of life has so far hardly been investigated. We will therefore develop a disease- and treatment-specific QoL-instrument.

Our study will result in follow-up data for at least three different surgery techniques allowing us to descriptively compare the results and possibly to establish criteria for the method of choice for a specific patient in the future or to stimulate the conductance of a head-to-head comparison in an RCT setting. Moreover, we will compare the results obtained in this study with those obtained in the US- Teen-LABS study
[39].

### Subproject 4

In subproject 4 “Economic aspects of extreme obesity in adolescents” of YES we will analyze the economic burden of extreme obesity in adolescents. This research project will investigate the impact of extreme obesity on healthcare utilization, costs and health related quality of life in a cohort of adolescents. An additional focus is the economic evaluation of a bariatric surgery intervention for adolescents with extreme obesity.

The first aim of this subproject is to measure, value and analyze all relevant direct and indirect costs, to describe differences between BMI categories among obese adolescents as well as first results on pre-post interventional differences.

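### Subproject 3 offers a descriptive comparison of non-randomised surgical techniques, on absolute BMI change, as a possible basis for criteria to choose a technique; it should account for BMI at surgery and serve only to generate hypotheses

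*Protocol article*

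**What the plan says.** All of this is in the protocol article, mainly under the heading Subproject 3.

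- **Endpoint.** "The primary endpoint of SP3 is weight change defined as difference between BMI at date of surgery and 12 months after". The reason given is comparability: "This outcome choice is in accordance with the outcome of the Teen-LABS study".
- **Comparison of techniques.** The study expects data on "at least three different surgery techniques allowing us to descriptively compare the results and possibly to establish criteria for the method of choice". The sentence applies such criteria to the individual patient at some later time, and gives as its other use the prompting of a randomised trial that compares techniques directly.
- **External comparison.** "we will compare the results obtained in this study with those obtained in the US- Teen-LABS study".
- **Adjustment.** The one method named is for the non-operated controls, who declined the pre-surgery programme or "declined surgery after completion of the pre-surgery program using propensity-score methods". The section also plans to relate patient characteristics and features of the operation to risks and to change in patient status, without describing a model.
- **Expected differences between techniques.** The Background says of earlier results: "In general, gastric banding resulted in less weight loss in comparison to bypass operations".
- **Caveats.** The third objective of Subproject 3 concedes that its effect estimates may be biased. The Discussion says the conclusions are limited by the observational design, and that randomised trials may prove necessary.

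**The concern.** The article states a method for comparing techniques (descriptive) and a possible use for the result (criteria for choosing a technique for a given patient). The use asks more than the method can give. No randomisation of technique is described, so the technique groups may differ in starting BMI, age, sex or centre. A descriptive contrast carries those differences into the result.

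The scale adds to the problem. The extreme group is defined by a BMI of at least 35 kg/m² with no upper limit, so BMI at surgery can vary widely. Absolute BMI change is sensitive to that starting value if patients tend to lose a similar fraction of their weight.

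At stake is a statement about which technique suits which adolescent that may partly reflect who received each technique. The comparison with the US Teen-LABS study has a related weakness: sharing an outcome aligns the measurement, but not the mix of techniques or of starting BMI.

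**Working it through.** Subproject 3 states no sample size, effect size, standard deviation or number per technique, so there is no figure of the plan to reproduce. The arithmetic below uses assumed inputs and shows only how the mechanism works.

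**1. Starting BMI and absolute change**

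Let B be mean BMI at surgery and r the relative BMI loss at 12 months, taken as equal for two techniques. Absolute loss is r × B, so the difference between techniques is r × (B₁ − B₂), although neither technique is better.

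| Assumed relative loss r | Gap in B of 5 kg/m² | Gap in B of 10 kg/m² (50 v 40) |
|---|---|---|
| 20% | 0.20 × 5 = 1.0 | 0.20 × 10 = 2.0 |
| 25% | 0.25 × 5 = 1.25 | 0.25 × 10 = 2.5 |
| 30% | 0.30 × 5 = 1.5 | 0.30 × 10 = 3.0 |
| 35% | 0.35 × 5 = 1.75 | 0.35 × 10 = 3.5 |

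If absolute loss did not depend on starting BMI, the difference from this source would be zero. The result rests on the assumption of similar relative loss.

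The ranking can also reverse. A technique with 25% loss used at a mean BMI of 50 gives 0.25 × 50 = 12.5 kg/m². One with 30% loss used at a mean BMI of 40 gives 0.30 × 40 = 12.0 kg/m². The first looks better on absolute change and is worse on relative change.

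**2. Mix of techniques and any overall figure**

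This matters for the external comparison. Let s be the share of banding, and assume a mean loss of 8 kg/m² with banding and 14 kg/m² with bypass. The overall mean loss is s × 8 + (1 − s) × 14.

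- s = 20%: 0.2 × 8 + 0.8 × 14 = 12.8 kg/m²
- s = 80%: 0.8 × 8 + 0.2 × 14 = 9.2 kg/m²

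Two cohorts with identical results per technique would differ by 12.8 − 9.2 = 3.6 kg/m². With a 40-point difference in shares and a technique difference of 3 to 8 kg/m², the gap is 0.40 × 3 = 1.2 to 0.40 × 8 = 3.2 kg/m². The Background supports the direction (less loss with banding) but gives no figures.

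**3. Which comparison has which method**

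| Comparison | Method stated |
|---|---|
| Operated v non-operated | Propensity score |
| Technique v technique | Descriptive |
| This study v Teen-LABS | None stated |
| Patient and operation features v outcome | Associations, model not described |

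The second row is a stated choice, not mere silence. The fourth might be built to adjust technique for patient characteristics, but the text does not say so.

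**The case against.** The case against is substantial, and much of it stands.

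- **Pooling.** A reader might infer that all techniques are merged into one primary estimate. The article defines one outcome variable but specifies no pooled estimator, and it expects results for each technique. The inference is not supported.
- **Setting the method of choice.** A reader might infer that the sponsor will fix the preferred technique from these data. The sentence speaks only of possible criteria, places them in the future and offers a randomised trial as the other use. That reading is too strong.
- **Misreading as technique effects.** To say that case mix will be taken for a technique effect is a prediction. The comparison is called descriptive, the estimates are conceded to be possibly biased, and the Discussion repeats the limits of the design.
- **How technique is chosen.** A reader might assume that it follows the patient or the collaborating surgical unit. The article does not say how it is chosen.
- **Missing detail.** Covariates, stratification and the method of the external comparison are commonly left to the full protocol or analysis plan. Their absence here is no finding.
- **Endpoint.** Absolute BMI change has a stated reason, and percent change can be computed from the same data.

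One thing survives. The criteria and the randomised trial are joined as alternatives, so the wording allows criteria without the trial. A hedge and a general caveat do not make a descriptive contrast of non-randomised techniques a sound basis for patient-level choice.

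**Conclusion.** The concern holds in a limited form, with low severity. The descriptive comparison of techniques on absolute BMI change is too weak for even tentative criteria for choosing a technique for a patient, because differences in starting BMI could look like differences between techniques.

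The illustrative size is 1.25 to 1.5 kg/m² for a 25 to 30% loss and a 5 kg/m² gap in mean starting BMI. This rests on similar relative loss across patients and on that gap existing, and the article supplies neither input. The actual bias cannot be sized from the documents and could be nil. The point about the external comparison is secondary: its result would depend on the mix of techniques, but how it will be handled may properly be set out elsewhere.

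**What to change.** 1. Report the 12-month BMI change by technique, with BMI at surgery and the number of patients beside it.
2. Where techniques are compared, adjust at least for BMI at surgery, and show percent BMI change as a supporting measure. The primary endpoint itself can stay as it is.
3. Limit the stated use of the comparison to generating hypotheses for the randomised head-to-head trial that the same sentence names, and drop the claim that it may yield criteria for choosing a technique.
4. Where the mix of techniques differs from that in Teen-LABS, present the external comparison by technique as far as its published data allow.

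The first two steps need only the BMI values that the endpoint already requires. The cost is a little more analysis, wider intervals per technique and a more modest claim. Adjustment for BMI at surgery will not remove confounding by other or unmeasured factors, so the third step is needed even if the second is done.
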